### Study procedure

Informed consent is obtained from all study participants in accordance with the Helsinki Declaration and approved by the UCSF Committee in Human Research (#11-06294). During the informed consent process, participants’ understanding of the information provided is assessed through a series of multiple choice questions with required responses before being able to proceed with the study. Questions are based on those used in studies with potentially vulnerable populations [41, 42]. Any wrong answers during the consent process are sent to study staff who then contact a potential participant via email or Facebook for further clarification of the consent process. Therefore, no participant will be enrolled that has not answered all consent questions correctly. Participants consenting to participate in the study are asked to verify age by sending proof through email or social media. Verified participants are emailed a baseline assessment. Those completing the baseline assessment are randomized to receive either the Tobacco Status Project (TSP) intervention of referral to the Smokefree.gov website (control).

A stratified random assignment program was developed and participants are assigned from within stratified blocks immediately after completing the baseline assessment. Participants are stratified on stage of change (precontemplation, contemplation, preparation) and smoking pattern (daily vs. non-daily), variables known to be related to outcomes and addressed by the intervention [43]. Participants in the TSP group are assigned to “secret” (private) Facebook groups based on their readiness to quit tobacco. Groups begin when there are approximately 10 participants enrolled, as that has been deemed the optimal number based on analyses of engagement in our previous work [37] ([name], [name], [name]: Smoking cessation intervention on Facebook: Which content generates the best engagement?, submitted). Participants in the control condition are given a referral to the Smokefree.gov program and are encouraged to use it as much as they would like.

Assessments occur online using the survey program Qualtrics at baseline, 3, 6, and 12 months follow-up. Participants receive their choice of gift cards in the amount of $20 per assessment, and a $20 bonus for completing all three assessments, for a total possible stipend of $100 for completing all assessments.

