### Treatment conditions

#### Tobacco Status Project (TSP)

The TSP is a smoking cessation intervention implemented entirely through “secret” (Facebook’s word for entirely private) Facebook groups. All TSP participants are assigned to a Facebook group based on their TTM stage of change (precontemplation: not ready to quit in the next 6 months; contemplation: intending to quit in the next 6 months; or preparation: ready to quit in the next month and demonstrating at least one past year quit attempt).

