The group-based intervention has three main features. First, evidence-based strategies have been used to design Facebook posts to be delivered each day for 90 days to intervention groups on Facebook. Posts are based on the US Clinical Practice Guidelines for smoking cessation [2] and the Transtheoretical Model (TTM) of behavior change [44], both recommending treatment be tailored to participants’ readiness to quit, and have been determined to be helpful to and likable by young adults ([name], [name], [name], [name]: Feasibility and quit rates of the “Tobacco Status Project”, submitted). Precontemplation group posts are based on Motivational Interviewing (MI), a directive patient-centered counseling intervention recommended by the Clinical Practice Guidelines [2, 45]. Posts elicit clients’ motivation and importance of changing tobacco use, problems associated with use, and using open-ended questions to elicit “change talk” (a client’s mention of desire, ability, reason, or commitment to change) through using the 5-R’s: relevance, risks, rewards, roadblocks, and repetition, shown to increase likelihood of tobacco quit attempts [46, 47]. Contemplation group posts incorporate MI and the TTM processes of self-liberation (e.g., making a commitment to quit), stimulus control (e.g., removing smoking paraphernalia from the home), and counter conditioning (e.g., engaging in alternative behaviors) are emphasized. Preparation group posts incorporate skills from cognitive behavioral therapy, found effective for long-term smoking cessation [48], as well as the TTM processes of self-liberation (e.g., making a commitment to quit), stimulus control (e.g., removing smoking paraphernalia from the home), and counter conditioning (e.g., engaging in alternative behaviors). Posts also encourage setting a quit date and making a detailed quit plan. Facebook posts include a combination of images, videos, text and polls designed to reflect the experience of young adults and all elicit a response from participants. Posts may suggest that participants use their FB or real social networks for support with alcohol or tobacco reduction. However, they are not required to share any information about substance use on social media. Figure 2 provides sample posts for each stage of change.

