### Power calculation

Previous trials of stage-based interventions for smoking cessation [53–57] and trials of Internet interventions for smokers motivated to quit [11, 58] suggest that quit rates for motivated smokers may be as high as 20 % (treatment) and 9 % (control). However, as this will be the first stage-based intervention for young adult smokers delivered over Facebook, and cessation rates in some Internet trials have been as low as 7 % point prevalence abstinence at 3 month follow-up [59], the conservative estimate of 10 % (treatment) and 5 % (control) 7-day point prevalence abstinence at 3, 6, and 12 months follow-up was made. Further, attrition in Internet cessation trials has tended to be as high as 50–75 % at 3 and 6 months follow-up [11, 12, 59]. With 50 % attrition at each time point, and at least one covariate (depending on group differences), a sample size of 480 will provide a minimal power level of .80, and a Type-I error rate of .05 to detect these cessation rates in the most conservative outcome of the study - 7-day point prevalence abstinence.

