### Data analysis

#### Primary analyses

Preliminary analyses will describe and summarize all measures and test the correlation between order of study entry and outcome rates of dropout by condition. If differences for any of these variables are noted, they will be statistically controlled as covariates in model testing. Missing data will be minimized through online assessment. When subjects do not complete online assessments, they will be re-contacted through Facebook or email to obtain missing information. For each hypothesis test, two sets of outcome analyses will be conducted - one with all participants who are maintained in the study, and another based only on biochemically verified smoking abstinence rates to allow for direct comparison of findings with the research literature.

The primary outcome of biochemically-verified 7-day abstinence will be compared between participants in the TSP and Control groups at 3- through 12-months follow up using a mixed-effects statistical model [60, 61]. The independent variables will be intervention versus the control condition, assessment point, plus covariates identified in preliminary analysis. The model will be estimated using maximum likelihood estimation.

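### TSP is delivered in Facebook groups of about 10 and controls are ungrouped, but neither the stated primary model nor the power calculation accounts for group; standard errors will be too small if outcomes correlate within groups

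*Protocol article*

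**What the plan says.** **Allocation.** Under Study procedure, "participants are assigned from within stratified blocks immediately after completing the baseline assessment". The strata are stage of change and daily versus non-daily smoking. The unit of randomisation is the individual.

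**Delivery in the TSP arm.** "All TSP participants are assigned to a Facebook group based on their TTM stage of change", and "Groups begin when there are approximately 10 participants enrolled". The section on TSP opens its description with "The group-based intervention has three main features". Members of a group share the daily posts, the comment threads, the weekly live sessions and, in preparation groups, CBT events scheduled separately for each group. Whole groups are randomised to one of four incentive conditions.

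**Delivery in the control arm.** Each participant is referred individually to Smokefree.gov. No groups are formed.

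**Primary analysis.** A mixed-effects model fitted by maximum likelihood: "The independent variables will be intervention versus the control condition, assessment point, plus covariates identified in preliminary analysis". The random effects are not named.

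**Power.** The Power calculation section takes "the conservative estimate of 10 % (treatment) and 5 % (control) 7-day point prevalence abstinence", then "With 50 % attrition at each time point, and at least one covariate", and concludes that "a sample size of 480 will provide a minimal power level of .80, and a Type-I error rate of .05". It contains no ICC or design effect.

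**Incentive comparison.** The Secondary analyses section uses a Kruskal-Wallis test on comments and a Pearson chi-square test on abstinence, both across individual participants.

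**The concern.** This is a partially nested design: clusters in one arm, independent individuals in the other. People who share a counsellor session, a comment thread, a set of peers and an incentive rule may come to resemble each other in outcome. The protocol gives reasons to expect this. It chose the group size from engagement analyses, names social support as a strength of the medium, and tests whether a group-level incentive changes engagement and abstinence.

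A model that handles repeated assessments within a person but not persons within a group treats about 10 correlated outcomes as 10 independent ones. The TSP-arm variance is then understated, so the interval for the main comparison is too narrow and the p-value too small. The Discussion says significant results would be strong evidence of efficacy, and that needs valid standard errors. For the incentive comparison the mismatch is plainer: the group is the randomised unit and the person is the unit of analysis.

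**Working it through.** **Inputs from the protocol article.** N = 480; 10% versus 5% abstinence; alpha .05; 50% attrition; groups of about 10.

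**Assumptions.** 1:1 allocation (the ratio is not stated), hence 240 per arm and 240/10 = 24 TSP groups; two-sided testing; ICC of 0.01, 0.05 and 0.10, because the documents give none.

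**The plan's own figure first.** For one time point with no clustering, power = Φ[(0.05 − 1.96·SE0)/SE1], where SE0² = 2(0.075)(0.925)/n and SE1² = [(0.10)(0.90) + (0.05)(0.95)]/n.
- n = 240 per arm: SE0 = 0.02404, SE1 = 0.02394, power 0.55.
- n = 120 per arm (50% attrition): SE0 = 0.03400, SE1 = 0.03385, power 0.31.

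The stated .80 is not reproduced even before clustering. That is a separate and larger matter; here it only sets the baseline.

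**Design effect, TSP arm only.** DE = 1 + (m − 1)·ICC. The true SE divided by the SE that ignores groups, with equal arms and equal rates, is R = √[(DE + 1)/2]. Actual two-sided type I error is 2[1 − Φ(1.96/R)].

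| m analysed per group | ICC | DE | R | SE understated (1 − 1/R) | Type I error |
|---|---|---|---|---|---|
| 10 | 0.01 | 1.09 | 1.022 | 2% | 5.5% |
| 10 | 0.05 | 1.45 | 1.107 | 10% | 7.7% |
| 10 | 0.10 | 1.90 | 1.204 | 17% | 10.4% |
| 5 | 0.01 | 1.04 | 1.010 | 1% | 5.2% |
| 5 | 0.05 | 1.20 | 1.049 | 5% | 6.2% |
| 5 | 0.10 | 1.40 | 1.095 | 9% | 7.4% |

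A beta-binomial simulation (100,000 runs, 24 groups against independent controls, common rate 5% or 10%) gave 5.4–5.5%, 7.5–7.8% and 10.3% for m = 10, and 5.1–5.5%, 5.8–6.3% and 6.9–7.4% for m = 5. This agrees with the formula.

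**If TSP works on average.** At 10% versus 5%, R becomes √[(0.09·DE + 0.0475)/0.1375], which is 1.03, 1.14 and 1.26 for m = 10. The interval is then too narrow by 3%, 12% and 21%.

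**Power with clustering.** With SE0² = (0.075)(0.925)(DE + 1)/240 and SE1² = (0.09·DE + 0.0475)/240, single-time power falls from 0.55 to 0.53, 0.47 and 0.41. With the unpooled SE1 in both places, the last two are 0.45 and 0.38.

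**Incentive comparison.** 24 groups over four conditions is about 6 randomised units per condition, analysed as about 60 independent people. Clustering here affects every condition, so the 3-df chi-square statistic is inflated by roughly DE. The rejection rate is approximately P(χ²₃ > 7.815/DE): 6.7%, 14.5% and 25% for m = 10, and 5.7%, 8.9% and 13.4% for m = 5.

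**The case against.** Four objections deserve an answer.

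**A group term is not excluded.** The quoted sentence lists independent variables, which are fixed effects. A random intercept for group would not appear there, and the participant intercept does not either. A condensed article may leave the random-effects structure to the analysis plan. This stands: a reader might infer that the model definitely omits group, and the text does not establish that. But nothing points to a group term. The power section allows for attrition and a covariate but not for clustering, and the incentive tests are written out at participant level although the group was randomised.

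**The type I error need not be inflated.** Individuals are randomised and groups are formed afterwards. If TSP changes nobody's outcome, membership creates no dependence. A simulation of that strict null with 240 per arm and assumed abstinence of 2%, 5% and 12% by stage gave 5.0% rejection under simple and 4.7% under stage-stratified randomisation. This stands too. The inflation needs group effects that exist and average to zero. The narrow interval, however, needs only that group effects differ, whether or not their average is zero.

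**Sorting by stage looks like a source of correlation.** For the main comparison it adds little, because randomisation is stratified on stage in both arms. For the incentive comparison it can matter, because groups are the randomised unit and each is built from one stage.

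**The size is uncertain.** An ICC of 0.10 has no support in the documents, and the planned attrition shrinks the effect. Both are correct, which is why the results are shown as a range and for both group sizes.

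**Conclusion.** The point holds conditionally. The design is partially nested, and no stated analysis or sample-size step accounts for Facebook group. If outcomes correlate within groups, standard errors for TSP versus control will be too small and the error favours declaring efficacy. Over assumed ICCs of 0.01 to 0.10, type I error runs from about 5.5% to 10% with full groups and from about 5.2% to 7.4% with half of each group analysed. At ICC 0 the bias vanishes, and at 0.01 it is small. It would go too far to say that the primary test certainly exceeds .05: that would need an ICC that the documents do not give, a model known to omit group, and a null with group effects averaging to zero.

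The incentive comparison rests on firmer ground, because there the randomised unit and the unit of analysis differ on the face of the text. Overall this should be fixed before analysis, but it is not the plan's most serious weakness; the unreproduced power figure is larger.

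**What to change.** 1. In the primary model, name the random effects: a participant intercept for repeated assessments and a Facebook-group intercept in the TSP arm only, with controls as singletons. A cluster-robust variance is an acceptable alternative. Either way, use a small-sample correction based on the number of groups, about 24 under 1:1 allocation.
2. Use the same structure in the secondary models that compare TSP with control.
3. Analyse the incentive comparison with the Facebook group as the randomised unit, either on group summaries or in a model with a group random effect.
4. Report the estimated ICC, and include a design effect when power is restated.

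If a group effect is already intended, one sentence settles items 1 and 2. Group assignment is a trial procedure and should be on record, so the cost is analysis wording, slightly wider intervals, and a frank view of how little information about 6 groups per incentive condition carry. The choice should be fixed before outcomes are seen, because whether group is modelled could decide a borderline primary p-value.

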### Secondary analyses

Mixed effects logistic and multinomial regression models for longitudinal ordinal response data to model secondary outcomes for tobacco use and across time (3, 6, 12 months): 1) reduction of cigarettes by 50 % or more (y/n), 2) tobacco quit attempt (y/n; 2 models), 3) action or maintenance stage of change (y/n); and 4) commitment to abstinence (y/n). Independent variables in all models will be treatment condition, abstinence status, and covariates identified as relevant to smoking characteristics in the literature.

To evaluate the secondary aim (effect of a monetary incentive on engagement in the TSP condition), we will test for differences in engagement and primary smoking outcome by incentive groups and the relationship between engagement and primary smoking outcome at 3 months. First, due to expected skewed distribution of the engagement variable (comments), the non-parametric Kruskal-Wallace test will examine overall differences in total number of comments made to the Facebook study group by incentive condition, with test for a linear trend in commenting by incentive frequency. Second, Pearson’s chi-square test will examine 7-day point prevalence abstinence by incentive condition. Abstinence rates will be examined by incentive group. Two sets of analyses will be conducted: one for biochemically verified abstinence, and one for reported abstinence. Finally, Mann–Whitney U tests will compare comments for those abstinent at 3months to those non-abstinent. Again, two sets of analyses will be conducted (one for biochemically-verified abstinence and one for reported abstinence).

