## Aims and hypotheses

### Main Aim: To evaluate the efficacy of the Facebook-based intervention for young adults in a randomized controlled trial

Hypotheses are:Participants receiving the intervention will have higher 7-day point prevalence abstinence at 3-, 6-, and 12-months follow-up compared to those in the control condition.Participants in the intervention condition will demonstrate greater reduction in cigarettes smoked and increased commitment to abstinence at 3-, 6-, and 12-months follow-up than those in the control condition.Participants in the intervention condition will be more likely to make a quit attempt during the 12-month study period compared to those in the control condition.

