### Inclusion criteria

Participants are required to meet the following criteria in order to be eligible for enrollment in the trial:English literate (at an 8^th^ grade reading level);age 18 to 25 years (consistent with the definition of young adulthood used by the National Survey of Drug Use and Health, and age range with the highest smoking prevalence nationally [38]);access to a digital camera that can take and send a picture (e.g., camera phone);go on Facebook “most” (≥4) days per week;≥100 cigarettes smoked in their lives; and currently smoking at least 1 cigarette per day on 3 or more days of the week. Smoking criteria are based on those used in the National Health Interview Survey and are liberal based on smoking patterns most common in young adults and to include ethnic/racial minority populations, who tend to smoke fewer cigarettes per day than Caucasians [1].

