### Measures

#### Primary outcome

The primary outcome biochemically-verified 7-day point prevalence abstinence at 3, 6, and 12 months. Participants reporting “no smoking, not even a puff” in the past 7 days will be coded as abstinent from cigarettes. At each follow-up assessment, participants reporting 7-day abstinence will be mailed a saliva cotinine test kit and asked to record two pictures: one giving a saliva sample, and another of the test result. Participants with a salivary cotinine level <11 ng/ml, indicating nonsmoking [50], will be considered confirmed nonsmokers. If participants indicate use of an electronic nicotine delivery-system to aid in smoking cessation, saliva cotinine and reported ENDS use will be recorded and reported separately from biochemically verified abstinence.

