### Secondary outcomes

The following secondary outcomes will be assessed at each timepoint:**Reduction of cigarette consumption by 50 % or more (y/n)** between baseline each follow-up will be calculated from the number of cigarettes smoked in the past 7 days at each time point.**Tobacco quit attempt** (y/n). A *Follow-up Smoking Questionnaire* will assess the presence and number of 24 h quit attempts since the last assessment, used to calculate presence of at least one quit attempt in the assessment time period.**Readiness to quit tobacco** will be assessed using the *Stages of Change Questionnaire*, [44] categorizing participants into five stage categories at each timepoint (precontemplation, contemplation, preparation, action, and maintenance), and predictive of quit attempts and cessation [51]. Outcome will be measured as proportion in action or maintenance stage sof change at 3, 6, and 12 month assessments.**Abstinence goal** will be assessed with the *Thoughts About Abstinence Form, *[52]*,* categorizing goal as no goal, intermediary goal (e.g., reduced smoking), or total abstinence. Outcome will be measured as proportion endorsing a goal of abstinence at each timepoint.**Engagement in TSP** will be measured by total number of comments to Facebook study groups during the three-month intervention period.

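### All secondary models adjust for abstinence, which arises only after randomisation and is the primary outcome, so they do not estimate the between-arm effects hypothesised

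*Protocol article*

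**What the plan says.** In the protocol article, Secondary analyses gives one covariate rule for every secondary model: "Independent variables in all models will be treatment condition, abstinence status, and covariates identified as relevant to smoking characteristics in the literature". The models cover "1) reduction of cigarettes by 50 % or more (y/n), 2) tobacco quit attempt (y/n; 2 models), 3) action or maintenance stage of change (y/n"), with commitment to abstinence as the fourth outcome.

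Five other places bear on this rule:
- Inclusion criteria require that participants are "currently smoking at least 1 cigarette per day on 3 or more days of the week".
- Primary outcome: "The primary outcome biochemically-verified 7-day point prevalence abstinence at 3, 6, and 12 months". Its self-report component is "Participants reporting “no smoking, not even a puff” in the past 7 days will be coded as abstinent from cigarettes".
- Secondary outcomes: the reduction endpoint "will be calculated from the number of cigarettes smoked in the past 7 days at each time point". For stage of change, "Outcome will be measured as proportion in action or maintenance". Quit attempts are counted in the interval between assessments. Abstinence goal is a stated intention.
- Main Aim, second hypothesis: "Participants in the intervention condition will demonstrate greater reduction in cigarettes smoked and increased commitment to abstinence" than control. The third hypothesis says that the intervention arm will be more likely to attempt to quit over the 12 months.
- Secondary analyses does not say whether abstinence status means verified or self-reported abstinence.

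**The concern.** The second and third hypotheses of the Main Aim are plain comparisons of intervention with control: does being assigned to the Tobacco Status Project (TSP) change reduction, commitment and quit attempts? That is a total effect. The article states no mediation or direct-effect aim for these endpoints.

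Abstinence lies on the path from the intervention to these endpoints. Holding it fixed takes out whatever part of the effect runs through quitting. It also means comparing, for example, those still smoking under TSP with those still smoking under control. These groups were formed by a response to treatment, so randomisation no longer makes them comparable. An intervention that works by getting people to quit could therefore show little or no benefit on outcomes that quitting produces.

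**Working it through.** The article gives no numerical result for the secondary models, so there is no figure to reproduce. The check reads the definitions against each other and then works out what the stated adjustment does.

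**Step 1: can abstinence status be a baseline covariate?** No. All participants smoke on at least three days a week at entry, so nobody is abstinent at baseline. A version lagged by one visit would be constant at 3 months and still post-randomisation afterwards.

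**Step 2: overlap with each endpoint.**
- Reduction of 50% or more: the cigarette count uses the same 7-day window as abstinence. Abstinent means zero cigarettes, a 100% reduction. The implication is strict.
- Quit attempt: at 3 months, a participant who smoked at entry and has not smoked for seven days has stopped for more than 24 hours since baseline. Taking such a stop as an attempt, it is implied. At 6 and 12 months it is not strictly implied, because someone continuously abstinent since before the previous visit may have no new attempt.
- Action or maintenance: the article defines the other three stages, all in terms of readiness to quit, but not these two. Heavy overlap is likely, but it is an inference.
- Abstinence goal: not implied.

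**Step 3: effect on the reduction endpoint.** Let a be the proportion abstinent in an arm and q the proportion of non-abstinent participants who reduce by 50% or more.

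- Proportion reaching the endpoint: p = a + (1 − a)q
- Unadjusted OR = [pT/(1 − pT)] / [pC/(1 − pC)]
- Adjusted OR = [qT/(1 − qT)] / [qC/(1 − qC)], because every abstinent participant reaches the endpoint in both arms and so carries no information on treatment.

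Inputs: a = 10% versus 5% (conservative) and 20% versus 9% (optimistic), from Power calculation. The value of q is an assumption guided by the feasibility figures at 12 months in Background (35% reduced by half; 9% verified and 18% reported abstinent): (35 − 9)/91 = 28.6%, taken as 28%, or (35 − 18)/82 = 20.7%. A value of 25% lies between. The 38% in the last row is purely illustrative.

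| Abstinent, TSP / control | q, TSP / control | p, TSP / control | OR unadjusted | OR adjusted |
|---|---|---|---|---|
| 10% / 5% | 28% / 28% | 35.2% / 31.6% | 1.18 | 1.00 |
| 10% / 5% | 25% / 25% | 32.5% / 28.75% | 1.19 | 1.00 |
| 10% / 5% | 20.7% / 20.7% | 28.6% / 24.7% | 1.23 | 1.00 |
| 20% / 9% | 28% / 28% | 42.4% / 34.5% | 1.40 | 1.00 |
| 10% / 5% | 38% / 28% | 44.2% / 31.6% | 1.71 | 1.58 |

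First row in full: 0.10 + 0.90 × 0.28 = 0.352; 0.05 + 0.95 × 0.28 = 0.316; OR = (0.352/0.648)/(0.316/0.684) = 1.18. Last row, adjusted: (0.38/0.62)/(0.28/0.72) = 1.58.

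In the first four rows TSP acts only through quitting, and the adjusted model returns a null. In the last row it also helps continuing smokers. A simulation of that row (1,000 runs, 240 per arm, one time point, full follow-up) gave ORs of 1.71 and 1.57, with power falling from about 0.81 to 0.61.

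**Step 4: an endpoint that abstinence does not imply.** Assume that 80% of abstinent and 30% of non-abstinent participants hold an abstinence goal in both arms, at 20% versus 9% abstinence. TSP: 0.20 × 0.80 + 0.80 × 0.30 = 0.400. Control: 0.09 × 0.80 + 0.91 × 0.30 = 0.345. Unadjusted OR = (0.400/0.600)/(0.345/0.655) = 1.27; within abstinence strata it is 1.00.

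**Step 5: stage.** If action or maintenance coincided exactly with abstinence, the unadjusted OR at 10% versus 5% would be (0.10/0.90)/(0.05/0.95) = 2.11, and no variation would remain within strata. If the covariate is verified abstinence and unverified quitters can be in action (assumed 12% versus 6% of those not verified), the effect stays estimable. Power in the same kind of simulation falls from about 0.84 to 0.56.

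**The case against.** The strongest reply is that the damage is bounded. The nulls in Step 3 are built in by assuming equal q in both arms, and with an effect among continuing smokers the OR only moves from 1.71 to 1.58. The unadjusted effect in the first row would itself be detected only about 14% of the time with 240 per arm, so little is lost in practice there. The primary model has abstinence as its outcome and is untouched. All of this stands, and it limits the size of the problem. It does not make the adjusted coefficient an answer to the stated hypotheses.

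A reader might also infer more than the article supports:
- That abstinence defines or implies every secondary endpoint. It does not for abstinence goal, nor strictly for quit attempts at 6 and 12 months, and the action and maintenance stages are not defined in the article.
- That the treatment effect cannot be estimated. Perfect prediction makes the abstinence coefficient diverge, but the treatment coefficient is still estimated from non-abstinent participants. It is lost only if an endpoint coincides with abstinence, which depends partly on whether verified or reported abstinence is used.
- That the effect would be reversed. Selection among continuing smokers could bias the comparison, but nothing in the article fixes its direction or shows a reversal.
- That leaving assessment point out of the covariate list is a further error. The same section describes longitudinal models over 3, 6 and 12 months, and a full term list is detail that an article commonly leaves out.

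**Conclusion.** The covariate rule is wrong as written. It is an explicit specification, not an omission, and no baseline reading of abstinence status is possible. The models for two of the three Main Aim hypotheses would estimate something other than the total between-arm effect, from a comparison no longer protected by randomisation.

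The size depends on how TSP works. If only through quitting, the reduction OR goes from about 1.18–1.23 to 1.00 at 10% versus 5% abstinence, and from 1.40 to 1.00 at 20% versus 9%. If it also helps continuing smokers, the effect is attenuated but remains estimable. These figures rest on the assumed reduction rates among non-abstinent participants and on a single time point with full follow-up; the mismatch with the hypotheses does not depend on them. The claim that the effect is always removed, or cannot be estimated, is not supported. The primary analysis is unaffected.

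**What to change.** Delete abstinence status from the secondary models that test the second and third Main Aim hypotheses. If the effect among continuing smokers, or an abstinence-adjusted model, is of interest, report it separately, labelled exploratory, and state whether abstinence is verified or self-reported. This changes one sentence and needs no new data.
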